## Abstract

**Background:**

Women with type 1 diabetes face particular demands in their lives in relation to childbearing. During pregnancy, in order to optimize the probability of giving birth to a healthy child, their blood glucose levels need to be as normal as possible. After childbirth, they experience a ‘double stress’: in addition to the ordinary challenges they face as new mothers, they also need to focus on getting their blood glucose levels normal. To improve self-management of diabetes and overall well-being in women with type 1 diabetes, a person-centered web-based support was designed to be tested in a randomized controlled trial (RCT) to be used during pregnancy and early motherhood. This protocol outlines the design of this RCT, which will evaluate the effectiveness of the specially designed web-based support for mothers with type 1 diabetes in Sweden.

**Methods/Design:**

The study is designed as an RCT. The web support consists of three parts: 1) evidence-based information, 2) a self-care diary, and 3) communication with peers. The primary outcome is general well-being evaluated with the Well-Being Questionnaire short version (W-BQ12) and diabetes management evaluated with the Diabetes Empowerment Scale, short version (SWE-DES). Women attending six hospital-based antenatal care centers in Sweden are invited to participate. The inclusion period is November 2011 to late 2014. The allocation of participants to web support (intervention group) and to usual care (control group) is equal (1:1). In total, 68 participants in each group will be needed to reach a statistical power of 80% with significance level 0.05.

**Discussion:**

The web support is expected to strengthen the women’s personal capacity and autonomy during pregnancy, breastfeeding, and early motherhood, leading to optimal well-being and diabetes management.

**Trial registration:**

ClinicalTrials.gov: NCT01565824 (registration date March 27th 2012).

## Background

Maternal type 1 diabetes complicates pregnancy, childbirth and the time just after childbirth. Consequences for the fetus/newborn include congenital malformations, miscarriages, growth anomalies and stillbirth, fetal macrosomia, operational deliveries, neonatal complications and also perinatal mortality. Maternal concerns include increased likelihood of worsened diabetes-related vascular complications, pre-eclampsia and eclampsia, and of caesarian section and vacuum extraction/forceps vaginal delivery [1, 2]. The degree of complications is mainly related to maternal glycemia, where abnormal blood glucose levels increase adverse outcomes. Optimized maternal normoglycemia from pre-conception through pregnancy is the most important tool available to minimize complications and increase the likelihood that a woman will give birth to a healthy child [1, 3]. During pregnancy, all women have a physiological need for more insulin than usual (up to two or three times more). For women with diabetes treated with insulin, this means that, in order to optimize the situation for the coming offspring, they need to parry the successively increased insulin need through intensive blood glucose controls and continuous insulin dose increases combined with a structured diet and activity plan [2–4]. Directly after childbirth the insulin need decreases, often to less than the pre-gestational levels [5].

Diabetes is unique in that much of the day-to-day responsibility for care rests with the individuals who have the disease. Our earlier research in Sweden has highlighted the vulnerable situation for women with type 1 diabetes in relation to childbearing. During pregnancy, they struggle day and night to achieve normal blood glucose levels in an attempt to ensure that the fetus/child will be born healthy; they typically experience frequent hypoglycemic episodes and feelings of stress, worry and insecurity [6–8]. It has been found that this demanding situation is worsened if care providers lack competence and also if the mothers feel left aside by healthcare workers who give more attention to the unborn child than to the women themselves. After childbirth, the intensive health care provided during pregnancy and childbirth is interrupted, placing the new mothers in a vulnerable situation as they experience unstable glycemia and more hypoglycemic episodes in relation to breastfeeding [8]. The mothers also described that they down-prioritized their own needs in favor of the child’s [9]. Compared to mothers without diabetes, they were more affected by daily life disruptions [10] and reported lower levels of well-being [11].

A structured literature review of 16 identified studies performed in Sweden, USA, Australia, Greece, Israel, Italy and the UK [12] has indicated similar results. Women with type 1 diabetes who were in transition to motherhood experienced a variety of psychosocial issues: increased levels of anxiety, diabetes-related distress, guilt, a sense of disconnectedness from health professionals, and a focus on the medicalization of pregnancy. A trusting relationship with health professionals, sharing experiences with other women with diabetes, active social support, and shared decision making and responsibilities for diabetes management helped them achieve a positive transition to motherhood. The authors concluded that health professionals can promote a positive transition to motherhood by proactively supporting women with type 1 diabetes in informed decision making, by facilitating communication with the health-care team and by coordinating care [12].

Thus existing research shows that the period of pregnancy, childbirth and early motherhood is characterized by an increased risk of complications in both the woman with type 1 diabetes and the fetus/child, and that the woman experiences a complex everyday situation and a lower sense of well-being. There is an obvious need for extended person-support - from professionals, family and friends and also peers, that is, mothers with similar experiences of diabetes and childbearing.

Our own research shows that the use of Internet communication is needed and expected by childbearing women with type 1 diabetes [13]. Therefore, we suggest that a person-centered web-based support - one that is available 24/7 and enables users to document their experiences and share in decision-making related to their care - as a complement to usual health-care arrangements may strengthen self-management capabilities and thus well-being in women with type 1 diabetes during pregnancy, childbirth and early motherhood. To our knowledge, such a person-centered web-based support has not yet been evaluated.

### Objective

This protocol outlines the design of a specially created web-based support system for women with type 1 diabetes during pregnancy and in early motherhood, tested in a randomized controlled trial (RCT).

## Methods/Design

### Study design

The study is labeled MODIAB-Web and is designed as an RCT to evaluate the effect of a web-based support system on well-being and diabetes management in the study group. An equal number of study participants, pregnant women with type 1 diabetes, will be included in the intervention group and control group (1:1). Web-based support will be offered to the intervention group as a complement to the usual diabetes and pregnancy care. Women allocated to the control group will receive the usual care. The study design is in accordance with the CONSORT recommendation for reporting pragmatic randomized controlled trials [14]. The flow of the RCT is illustrated in Figure 1.

**Figure 1 Fig1:**
[figure not shown]
**Flow diagram MODIAB-Web evaluating a web-based support for pregnant women and new mothers with type 1 diabetes mellitus in Sweden: study protocol for a randomized controlled trial.**

### Sample size estimation

Sample size estimation in this RCT is based on the two primary outcome variables: 1) general well-being measured by the Well-Being Questionnaire (W-BQ12) and 2) diabetes management measured by the Swedish Diabetes Empowerment Scale (SWE-DES). In order to detect a clinically relevant difference of 1.25 in well-being between the intervention group and the control group, 68 subjects will be needed in each group to reach a statistical power of 80%, assuming a SD of 0.40 in each group, with a significance level 0.05. Similarly, to detect a difference of 0.2 in diabetes management, 68 subjects will be needed in each group to reach a statistical power of 80%, assuming a SD of 2.5 in each group, with a significance level 0.05. A total sample size of 160 has been chosen to compensate for a probable 10% loss to follow-up.

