### Validity and reliability of instruments used

The research group has opted to use well-tested instruments as outcome measures whenever possible. All instruments have to be available in Swedish to be used in this study. In the primary outcome measurements the W-BQ12 has a described Cronbach’s alpha of >0.88 [19] and its validity is considered to be good. The other primary outcome scale, SWE-DES, is considered acceptable in terms of reliability (Cronbach’s alpha range of 0.68 to 0.91 in the 23-question version of the scale) [20, 24]. In terms of secondary outcome, the Sense of Coherence 13-item scale is recognized as a reliable and valid instrument that can be applied across different cultures (range of Cronbach’s alpha 0.70 to 0.92 in 127 studies) [21]. The SWE-PAID-20 questionnaire was reported to have a (Cronbach’s alpha of 0.94) [25]. The SWE-HFS scale has also been reported as having good reliability (Cronbach’s alpha 0.85) and validity [22].

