### Statistical analyses plan

The full analysis set, Intention To Treat population (ITT population), consists of all randomized patients who had at least one follow-up measurement. The Per-Protocol population (PP population) consists of all patients in the ITT population without any significant protocol deviations. The PP population is defined at the clean-file meeting before the database is locked. Primary efficacy analyses will be performed on our two primary variables general well-being (W-BQ12) total score and diabetes empowerment (SWE-DES) total score, both at six months after delivery between the two randomized groups using Fisher’s non-parametric permutation test on the full analysis set (ITT population), two-sided test on significance level 0.025. If significant differences in baseline variables are found between the two randomized groups, a complementary analysis of covariance (ANCOVA) will be performed adjusted for these baseline variables. Last observation carry forward (LOCF) will be applied from two months if the six months value is missing.

Statistical analyses will be conducted using SPSS, version 16.0, and SAS, version 9.2 (Cary, NC). All tests will be two-tailed and conducted at 5% significance level.

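### The W-BQ12 power calculation does not say which score its difference of 1.25 and SD refer to, and neither printed SD is plausible for the 12-item total score that is tested

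*Protocol article*

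**What the plan says.** Under Sample size estimation, the protocol article sets the W-BQ12 target with the words "In order to detect a clinically relevant difference of 1.25 in well-being between the intervention group and the control group", "assuming a SD of 0.40 in each group". The parallel sentence for the SWE-DES is "to detect a difference of 0.2 in diabetes management", "assuming a SD of 2.5 in each group". For each outcome it states that "68 subjects will be needed in each group to reach a statistical power of 80" per cent, at significance level 0.05.

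Under Statistical analyses plan, the first primary variable is "general well-being (W-BQ12) total score" at six months after delivery, tested two-sided at 0.025. Under Validity and reliability of instruments used, "the W-BQ12 has a described Cronbach’s alpha of >0.88", taken from a cited source.

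The article gives no item scoring, total range, expected mean or observed SD for the W-BQ12. It also gives no source for 1.25.

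**The concern.** A sample size for a total score needs a difference and an SD on that total score. Sample size estimation speaks only of well-being and does not name the score.

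The printed pairs are visibly wrong, because neither reproduces 68. The natural repair is to exchange the two SDs, so that both outcomes have a standardised difference of 0.5. That brings the calculation close to 68, but it leaves a W-BQ12 total score with an SD of only 2.5. For a sum of 12 items with high internal consistency, this is very little spread. A sponsor who only exchanged the SDs would leave a pair that still looks wrong for the endpoint.

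Two things depend on this. The 80% power claim is one. The other is the yardstick for reading the result: 1.25 points is presented as clinically relevant, and on a wider total score it would be well below half an SD.

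**Working it through.** **Inputs.** From Sample size estimation: differences 1.25 and 0.2, SDs 0.40 and 2.5, 68 per group, 80% power, level 0.05 (taken as two-sided, since the Statistical analyses plan makes all tests two-tailed). From the reliability section: alpha 0.88, the lower bound given. From the instrument's name: k = 12 items.

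**Step 1: the plan's own figure.** n per group = 2 × (1.960 + 0.842)² × (SD/difference)² = 15.70 × (SD/difference)².

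- W-BQ12 as printed: 15.70 × (0.40/1.25)² = 1.6, so 2 per group (3 by t-test).
- SWE-DES as printed: 15.70 × (2.5/0.2)² = 2453 per group. With 68 per group, power is about 7%.
- SDs exchanged (1.25/2.5 and 0.2/0.40, both 0.5): 15.70 × 4 = 62.8, so 63 per group (64 by t-test). Power at 68 per group is 82% to 83%.

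The stated 68 is not reproduced exactly in any of these. For a difference of 1.25 it needs an SD of about 2.58 (t-test) to 2.60 (normal). A 3/π inflation for a Wilcoxon test would bring 2.5 to 67–68, but the section mentions no such step. Of the printed SDs, 2.5 is the only one that comes near.

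**Step 2: what each SD implies for the items.** Cronbach's alpha is k/(k−1) × (1 − sum of item variances / total variance). Rearranged, the mean item variance is total variance × (1 − alpha × 11/12) / 12. At alpha 0.88 the bracket is 1 − 0.8067 = 0.1933.

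- Total SD 0.40: 0.16 × 0.1933 / 12 = 0.0026, item SD 0.05.
- Total SD 2.5: 6.25 × 0.1933 / 12 = 0.1007, item SD 0.32.

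If items are scored in integers and the departing answers differ by one category, p(1 − p) = 0.1007 gives p = 0.114. About 89% of women would then give the same answer to an average item.

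The cited alpha comes from another sample, so the result was checked against other values. With total SD 2.5, the item SD is 0.43 at alpha 0.70, 0.30 at 0.90 and 0.26 at 0.95. It stays small throughout.

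**Step 3: power for 1.25 on the total score.** Item scoring is not in the documents, so the item SD is an assumed range. Total SD = item SD × √(12/0.1933) = item SD × 7.88. Power is for a two-sample t-test with 68 per group, used as an approximation to the planned permutation test.

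| Assumed item SD | Total SD | 1.25 in SD units | Power at 0.05 | Power at 0.025 |
|---|---|---|---|---|
| 0.4 | 3.2 | 0.40 | 63% | 52% |
| 0.5 | 3.9 | 0.32 | 45% | 34% |
| 0.6 | 4.7 | 0.26 | 33% | 24% |
| 0.8 | 6.3 | 0.20 | 21% | 14% |
| 1.0 | 7.9 | 0.16 | 15% | 9% |

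**Step 4: what 68 per group can detect.** With 80% power, 68 per group detects 0.48 SD at two-sided 0.05 and 0.53 SD at 0.025. For total SDs of 3.2 to 7.9, 0.48 SD is about 1.5 to 3.8 points.

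**The case against.** The strongest case against has four parts.

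**A total SD of 2.5 with alpha 0.88 is not impossible.** A reader might infer that these figures cannot belong to the total score. That goes too far. A simulation of 12 integer items with about 11% of answers one category apart gave a total SD of 2.55 and alpha 0.895. Calling the combination implausible is a judgement about how women answer a well-being questionnaire, and the article gives neither the response range nor an observed SD that would settle it. This stands, and it limits the point to implausibility.

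**No subscale is documented.** It is tempting to conclude that 1.25 and 2.5 describe a shorter subscale, because four items with alpha 0.7 to 0.8 and SD 2.5 would have an ordinary item SD of 0.86 to 0.79. The article mentions no W-BQ12 subscale, so this explanation has no support in it. What can be said is that the score is not named.

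**The exchange of SDs is itself an inference.** The article prints 0.40 for well-being, and 2.5 does not give 68 exactly. The difference, the SD or the method could also be misprinted. This stands, but it does not rescue the calculation: 0.40 is even less plausible than 2.5, and an SD of about 2.6, which would give 68, raises the same question.

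**The power figures depend on an assumed item spread.** This is true, and the range is shown for that reason. Even its low end, an item SD of 0.4, falls short of 80%.

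**Conclusion.** The point holds as a failure to tie the W-BQ12 difference and SD to the score that is tested, with neither printed SD plausible for that score. It is separate from the apparent exchange of SDs and remains after the exchange is made.

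It is not shown that the target effect lies on a different scale from the endpoint. That is a suspicion, which the source of 1.25 or an observed SD would confirm or remove.

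In size, the stated 80% power for 1.25 points could be anywhere from 63% to 15% at two-sided 0.05, and from 52% to 9% at the 0.025 level of the primary analysis. The yardstick of 1.25 would be 0.40 to 0.16 SD instead of the 0.5 SD that the exchanged figures imply. This rests on 12 items (from the instrument's name), alpha 0.88 carrying over to this population, and item SDs of 0.4 to 1.0. If the observed total SD proves to be near 2.5, power at 0.05 is 82% to 83% and this concern falls away.

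**What to change.** 1. In Sample size estimation, state which W-BQ12 score 1.25 and its SD refer to, and their source.
2. Check the total-score SD on trial data pooled without arm. The T0 data serve first. Six-month data, also pooled without arm, should be added if available, because the SD in early pregnancy may differ from the SD at the endpoint.
3. Using that SD, restate in Sample size estimation and in the power sentence of the Abstract either the power for the relevant difference or the difference that 68 per group can detect with 80% power: about 0.48 SD at 0.05, or 0.53 SD at the 0.025 level of the primary test.
4. Justify the clinically relevant difference separately, on the total-score metric. The detectable difference must not take its place, because sample size does not determine clinical relevance.

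The cost is a text change and one descriptive calculation on data that the trial collects anyway. No extra participants are asked for, and pooling without arm reveals nothing about the treatment effect. The downside is that the stated power will probably look less favourable.

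### The 80% power is calculated at significance level 0.05, but the two primary outcomes are tested at 0.025; power is then about 74–77% at the planned size, if the two printed SDs were transposed

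*Protocol article*

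**What the plan says.** - **Sizing.** The section Sample size estimation treats the two primary outcomes separately, and each calculation arrives at the same number: "68 subjects will be needed in each group to reach a statistical power of 80" per cent. For W-BQ12 the difference is 1.25 ("In order to detect a clinically relevant difference of 1.25 in well-being between the intervention group and the control group"), "assuming a SD of 0.40 in each group, with a significance level 0.05". For SWE-DES the difference is 0.2, "assuming a SD of 2.5 in each group, with a significance level 0.05".
- **Abstract.** Methods/Design gives the same figure: "68 participants in each group will be needed to reach a statistical power of 80% with significance level 0.05".
- **Recruitment.** "A total sample size of 160 has been chosen to compensate for a probable 10% loss to follow-up".
- **Testing.** The Statistical analyses plan compares both primary variables at six months after delivery by Fisher's permutation test on the full analysis set, "two-sided test on significance level 0.025". The same section ends: "All tests will be two-tailed and conducted at 5% significance level".

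**The concern.** Two primary outcomes tested at 0.025 each share an overall 5% (2 × 0.025 = 0.05). That is a sound arrangement, but it makes each test harder to pass, and the sample size was worked out as if each could use the full 0.05. The advertised power therefore belongs to tests that the trial does not plan to run.

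This matters most for a null result. Readers will judge it against a one-in-five chance of missing the target effect, when the planned tests carry a larger one. Both significance levels are printed in the article, so the conflict does not come from detail left to a fuller document.

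**Working it through.** **Inputs.** Differences 1.25 and 0.2, SDs 0.40 and 2.5, level 0.05, power 80%, 68 per group, total 160 and 10% loss all come from Sample size estimation. The two-sided 0.025 comes from the Statistical analyses plan. Normal quantiles: 1.960 (two-sided 0.05), 2.241 (two-sided 0.025), 0.842 (80% power).

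**Formulas (normal approximation).** With d = difference/SD:
- n per group = 2(z_α + z_β)²/d²
- power = Φ(d√(n/2) − z_α)

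The t-test figures use the noncentral t distribution. The rank-test variant divides the t-test n by 0.955.

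**Step 1: the plan's figure from the SDs as printed, two-sided 0.05.**
- W-BQ12: d = 1.25/0.40 = 3.125, so n is 2–3 per group.
- SWE-DES: d = 0.2/2.5 = 0.08, so n = 2 × (1.960 + 0.842)²/0.08² ≈ 2,453 per group.

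Neither gives 68, and one-sided versions (2 and 1,933) do not either.

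**Step 2: the plan's figure with the SDs exchanged (an assumption).** 1.25/2.5 = 0.2/0.40 = 0.5 SD for both outcomes, which would explain why both share one n.
- Normal: 2 × (1.960 + 0.842)²/0.25 = 62.8, so 63 per group.
- t-test: 63.8, so 64 per group.
- Rank-test variant: 63.8/0.955 = 66.8, so 67 per group.

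Only the last comes close to 68. At 0.05, 68 per group gives 83.0% (normal), 82.5% (t-test) or 80.7% (rank-test variant). This is the only reading found under which 68 is plausible.

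**Step 3: power at two-sided 0.025, 0.5 SD.** Evaluable women after loss: 160 × 0.9 = 144, or 72 per group. For the normal approximation, d√(n/2) is 2.915 with 68 per group and 3.000 with 72.

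| Method | 68 per group | 72 per group |
|---|---|---|
| t-test | 74.1% | 76.8% |
| Rank-test variant | 71.9% | 74.6% |
| Effect set so that 68 gives exactly 80% at 0.05 | 71% | 74% |
| Normal approximation (slightly optimistic) | Φ(2.915 − 2.241) = 75.0% | Φ(3.000 − 2.241) = 77.6% |

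Simulation with 68 per group agrees: 74.0% (t-test), 75% (permutation test on means) and 71.6% (Mann-Whitney).

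**Step 4: n for 80% power at 0.025, 0.5 SD.** Normal: 2 × (2.241 + 0.842)²/0.25 = 76.04, so 77. t-test: 77.3, so 78. Rank-test variant: 77.3/0.955 = 81.0, so 81. Both 68 and 72 fall short by every method.

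**Step 5: detectable difference with 72 per group, 80% power, 0.025 (t-test).** d = 0.518, which is 0.518 × 2.5 = 1.30 on W-BQ12 and 0.518 × 0.40 = 0.207 on SWE-DES, if the SDs are 2.5 and 0.40.

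**Step 6: power at 0.025 with the SDs as printed, 68 per group.** W-BQ12 about 100%; SWE-DES about 4% (also 4% with 72).

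**The case against.** **The closing sentence of the analysis plan puts all tests at 5%.** Read literally, this matches the sample size section and removes the mismatch. The specific 0.025 for the primary variables is still the better reading, because it is attached to those analyses by name and fits two outcomes sharing 5%. The objection does show that the analysis plan contradicts itself. If the sponsor meant 0.05 for each primary outcome, the 0.025 is the error and the same sections still need reconciling.

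**The shortfall rests on an effect size the protocol does not print.** This stands. A reader might take 74% as the trial's power without qualification. The documents do not support that: the figure needs exchanged SDs, and the method behind 68 is not stated. Only a range under a declared assumption is defensible.

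**68 is not the planned size.** This also stands. The trial recruits 160 and expects to keep 72 per group, where the t-test shortfall is about 3 points (80 − 76.8 = 3.2). If no woman were lost, 80 per group would give 81.5%.

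**Pregnancy losses might lower power further.** A reader might infer this from the withdrawal criteria, which remove women after randomization for pregnancy loss or infant death. The article gives no rate. It also lets women who miscarry in the first trimester re-enter in their original group, says that miscarriage will prolong data collection, and carries two-month values forward. No further reduction can be put in figures from this text.

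**Conclusion.** The mismatch is in the text: sizing at 0.05, primary tests at two-sided 0.025. The stated 80% is not a property of the planned tests.

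If the SDs were transposed, power per outcome is about 71–75% with 68 per group and about 74–77% with the expected 72. The chance of missing a 0.5 SD effect at the planned size is then about 23% by t-test, against the 20% implied. That is a modest gap. If the SDs are as printed, the 80% is far too high for SWE-DES (about 4%) and far too low for W-BQ12. The figure for SWE-DES therefore fails on either reading.

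Two stronger conclusions are not supported. The first is that the trial must recruit more women: the gap at 72 per group is small under the transposition reading, and an honest restatement deals with it. The second is that baseline adjustment or a stepwise multiplicity procedure would recover the lost power: the article gives no baseline correlation or other figure from which to show that.

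**What to change.** Keep the total at 160 and make three changes to the text.

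1. **Sample size estimation:** confirm or correct which SD belongs to which scale.
2. **Sample size estimation and abstract:** restate power at two-sided 0.025. If the SDs are 2.5 (W-BQ12) and 0.40 (SWE-DES), 72 evaluable women per group give about 77% power per outcome by t-test for differences of 1.25 and 0.2. The differences detectable with 80% power are about 1.30 and 0.207. Name the method used.
3. **Statistical analyses plan:** limit the closing 5% sentence to tests other than the two primary ones.

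The cost is a few reworded sentences and a slightly less favourable power figure. Recruitment and the primary analysis do not change.

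### The SDs for the two primary outcomes appear to be exchanged, and neither power statement is true as printed

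*Protocol article*

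**What the plan says.** The section *Sample size estimation* of the protocol article bases the sample size on both primary outcomes.

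- **W-BQ12 (general well-being):** "In order to detect a clinically relevant difference of 1.25 in well-being between the intervention group and the control group", the article calls for 68 women per group at 80% power, "assuming a SD of 0.40 in each group, with a significance level 0.05".
- **SWE-DES (diabetes management):** "to detect a difference of 0.2 in diabetes management, 68 subjects will be needed in each group", again at 80% power, "assuming a SD of 2.5 in each group, with a significance level 0.05".

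The total is then set at 160 to allow for 10% loss. The Abstract repeats 68 per group, 80% power and 0.05. No other section gives an SD for either scale or changes the pairing. The paragraph does not say whether the test is one- or two-sided, but *Statistical analyses plan* does: "All tests will be two-tailed and conducted at 5% significance level".

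**The concern.** With the same allocation, power and alpha, two outcomes that need the same number per group must have the same standardised effect. The printed effects are 3.125 and 0.08, a ratio of about 39, so the two claims cannot both be true. The calculation below shows that neither is.

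These are the only planning assumptions the article gives for its primary outcomes. Taken at face value, the trial has almost no chance of detecting its SWE-DES target, and its W-BQ12 target is a shift of more than three SDs. A null SWE-DES result could then be read as the expected outcome of an underpowered comparison. Anyone comparing the observed SDs with the planned ones would use the wrong reference for both scales.

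**Working it through.** **Inputs.** All come from *Sample size estimation*, except the 1:1 allocation (*Study design*) and two-sided testing (*Statistical analyses plan*): differences 1.25 and 0.2; SDs 0.40 and 2.5; power 80%; alpha 0.05; stated n of 68 per group.

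**Formulas (normal approximation).**
- n per group = 2(z₀.₉₇₅ + z₀.₈₀)²/d² = 2(1.960 + 0.842)²/d² ≈ 15.70/d², where d = difference/SD.
- Power at n per group ≈ Φ(d√(n/2) − 1.960). With n = 68, √(n/2) = √34 = 5.831.

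Each result was checked against the two-sample t-test.

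**Step 1: can 68 be reproduced from the printed pairs?**

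| Outcome | d | n per group, normal | n per group, t-test | t-test power at 68 |
|---|---|---|---|---|
| W-BQ12 | 1.25/0.40 = 3.125 | 15.70/9.766 = 1.6, so 2 | 2.9, so 3 | about 100% |
| SWE-DES | 0.2/2.5 = 0.08 | 15.70/0.0064 ≈ 2,453 | 2,454 | 7.5% |

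It cannot. The stated 68 is 23 to 34 times the W-BQ12 requirement, and the SWE-DES requirement is about 36 times 68 (2,453/68).

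**Step 2: does another convention rescue the figure?** One-sided testing and alpha 0.025 were also tried, alone and together. W-BQ12 stays between 2 and 4 per group and SWE-DES between 1,933 and 2,972. None comes near 68.

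**Step 3: what effect does 68 imply?** Solving 15.70/d² = 68 gives d = √(15.70/68) ≈ 0.48. The SDs that would fit are 1.25/0.48 ≈ 2.6 for a difference of 1.25, and 0.2/0.48 ≈ 0.42 for a difference of 0.2. These lie within about 4% of 2.5 and 0.40, the two printed SDs in the opposite order.

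**Step 4: exchange the SDs.**
- W-BQ12: 1.25/2.5 = 0.50.
- SWE-DES: 0.2/0.40 = 0.50.
- n per group = 15.70/0.25 = 62.8, so 63 (normal) or 64 (t-test), for both outcomes.
- Power at 68 = Φ(0.50 × 5.831 − 1.960) = Φ(0.955) = 83.0% (normal) or 82.5% (t-test).

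**Step 5: the remaining gap of four or five women.** The planned test is a non-parametric permutation test. If the planners allowed about 5% for this, 64 × 1.05 = 67.2, which rounds up to 68. Dividing by the relative efficiency of a rank test gives 64/0.955 = 67.0. The article states no such allowance, so this is an assumption, and the finding does not depend on it.

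**Step 6: the loss allowance.** This step is sound: 136/0.9 ≈ 151.1, so 152 women, and 160 less 10% leaves 144, which exceeds 136.

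**The case against.** The strongest objection is that the exchange of SDs is inferred. The arithmetic shows that 1.25 belongs with 2.5 and 0.2 with 0.40, but not which pair belongs to which scale. Exchanging the two differences instead would also give 0.50 for both outcomes, and the article gives neither the scoring nor the expected spread of either scale. The re-pairing also yields 63 or 64 per group, not 68. Finally, if this is a misprint, 68 per group still exceeds 80% power at 0.05, so the harm is to the text and not to the design.

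Much of this stands. The article names 1.25 as a clinically relevant difference in well-being, which favours exchanged SDs but does not prove it, so the correction has to wait for the source calculation. The gap to 68 is real, but it is small beside the error of the printed pairs: four or five women per group, against 68 for a need of 2 or 3 and 68 for a need of 2,453. It is also true that the article describes no interim SD review and does not use the planning SDs in the analysis, so no trial procedure runs on the wrong values.

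None of this makes the printed statements true. They are specific figures in running prose, so condensation or a broken table does not explain them, and they are the stated justification for the sample size on both primary outcomes.

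**Conclusion.** The concern holds. As printed, at two-sided 0.05, 68 per group gives about 100% power for W-BQ12, where 2 or 3 women would suffice, and 7.5% for SWE-DES, where about 2,453 would be needed. This part is arithmetic and needs no assumption beyond a standard comparison of two means.

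That the SDs were exchanged is a strong inference: it makes both standardised effects exactly 0.50 and brings the requirement to 63 or 64 per group. On that reading the design is intact at alpha 0.05, with 82.5% power at 68 per group, and the error lies in the written justification. It should still be corrected, because both primary outcomes rest on it and the power claim is repeated in the Abstract.

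**What to change.** 1. Retrieve the source calculation and confirm which SD belongs to which scale.
2. If it confirms the exchange, print SD 2.5 with the W-BQ12 difference of 1.25, and SD 0.40 with the SWE-DES difference of 0.2. State the common standardised effect of 0.50.
3. Say how 68 was reached from 63 or 64, for example by an allowance for the non-parametric test, if one was made.
4. Restate power at the alpha that the primary analysis will use. *Statistical analyses plan* tests each primary outcome at two-sided 0.025. With an effect of 0.50 that needs 77 (normal) or 78 (t-test) per group, and 68 gives about 74% to 75%. The mismatch of alphas is a separate issue, but it cannot be judged until the SDs are right.

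The cost is two corrected figures and a sentence or two in the protocol and any SAP. Correcting the SDs changes nothing in recruitment, data collection or the planned test.
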